# HAPPi Kneecaps! Protocol for a participant- and assessor-blinded, randomised, parallel group feasibility trial of foot orthoses for adolescents with patellofemoral pain

**DOI:** 10.1186/s13047-020-00417-9

**Published:** 2020-08-02

**Keywords:** Patellofemoral pain, Adolescents, Feasibility, Foot orthoses

## Abstract

**Background:**

Patellofemoral pain (PFP) is a common cause of knee pain in adolescents, but there are limited evidence-based treatment options for this population. Foot orthoses can improve pain and function in adults with PFP, and may be effective for adolescents. The primary aim of this study is to determine the feasibility of conducting a full-scale randomised controlled trial (RCT) evaluating the effects of contoured foot orthoses on knee pain severity and patient-perceived global change, compared to flat shoe insoles, in adolescents with PFP. The secondary aim is to provide an estimate of treatment effects for foot orthoses, compared to flat insoles, in adolescents with PFP.

**Methods:**

This randomised, controlled, participant- and assessor-blinded, feasibility trial has two parallel groups. Forty adolescents (aged 12–18 years) with clinical symptoms of PFP will be recruited from Queensland, Australia. Participants will be randomised to receive either prefabricated contoured foot orthoses or flat shoe insoles. Both interventions will be fit by a physiotherapist, and worn for 3 months. Feasibility will be evaluated through assessing willingness of volunteers to enrol, number of eligible participants, recruitment rate, adherence with the study protocol, adverse effects, success of blinding, and drop-out rate. Secondary outcomes will evaluate knee-related pain, symptoms, function, quality of life, global rating of change, patient acceptable symptom state, and use of co-interventions, at 6 weeks and 3 months. Primary outcomes will be reported descriptively, while estimates of standard deviation and between-group differences (with 95% confidence intervals) will be reported for secondary outcomes.

**Discussion:**

Findings of this study will inform the feasibility of a full-scale RCT investigating the efficacy of contoured foot orthoses in adolescents with PFP. This full-scale study is necessary to improve the evidence base for management of adolescent PFP, and enhance outcomes for this population.

**Trial registration:**

ACTRN12619000957190.

## Background

Knee pain is responsible for considerable health impact in adolescents, with patellofemoral pain (PFP) one of the most common knee pain conditions affecting this population [1]. PFP affects almost 30% of adolescents [2], and can have substantial detrimental effects. These include reduced participation in sport and physical activity, which can have implications for general health, mental health and overall quality of life [3–5]. Paellofemoral pain in adolescents tends to be persistent [5], with one-quarter of adolescents experiencing ongoing PFP symptoms well into adulthood [6]. Together, this highlights the importance of optimal management of PFP in adolescents, to avoid ongoing symptoms and disability across the lifespan.

Despite the burden of adolescent PFP, very few studies have investigated treatments for this population. Only two randomised controlled trials (RCTs) have been conducted in adolescents with PFP, which evaluated exercise and patient education [7], and soft foot orthoses [8]. Due to the lack of direct evidence, clinicians involved in the management of adolescents with PFP tend to apply treatment guidelines based on evidence from adult studies [9]. However, adolescents are a unique population with their own physical and psychosocial characteristics [10] – they are not simply small adults. For example, adolescents with PFP do not demonstrate the same quadriceps and hip strength deficits as adults with PFP [10], especially in early adolescence (age 12–16 years) [11]. Evidence-based treatments evaluated in adult PFP cohorts may have different efficacy in adolescents with PFP. While successful outcomes with exercise therapy and multimodal physiotherapy (exercise combined with patellar taping and manual therapy) are observed in 62–81% of adults with PFP after 12 months [12, 13], only 38% of adolescents with PFP experience a successful outcome with a similar intervention [7, 10]. Adolescents with PFP also have lower success with exercise therapy (53%) compared to adults (67%) [10]. Poorer outcomes in adolescents could be attributable to lower adherence with home exercise programs [10]. There are a number of potential barriers to exercise adherence in adolescents, including competing priorities (e.g. school, sport and social commitments) and the high prevalence of bilateral PFP (which doubles exercise dose/time) [10].

Foot orthoses may be an effective intervention for adolescents with PFP. Worn bilaterally, foot orthoses have the potential to exert biomechanical and physiological effects on the lower limb during weight bearing activities, which typically aggravate PFP [14]. Foot orthoses are a recommended intervention for adults with PFP [9]. In our previous RCT, prefabricated contoured foot orthoses resulted in significantly greater global improvement than flat insoles over 6 weeks (number needed to treat 4, 95% CI 2 to 51) [12]. Compared to flat insoles, foot orthoses resulted in faster symptom improvement in adults with PFP, which is important given that symptom severity and duration are key determinants of long-term prognosis [15, 16]. Investigating the efficacy of foot orthoses in an adolescent population is needed to inform clinical guidelines specifically for adolescents with PFP.

Considering the expense and time required to run a full scale RCT, it is necessary to first determine feasibility. There has been only one previous RCT assessing the effects of foot orthoses in adolescents with PFP, published in 1993 [8]. The results demonstrated a greater reduction in PFP symptoms with soft foot orthoses and an exercise program, compared to flat shoe inserts and exercise. However, the results should be considered with caution given that the method of foot orthoses prescription does not reflect current clinical practice [17], that only females were included in the study cohort, and the small sample size (*n* = 20).

The primary objective of this study is to determine the feasibility of conducting a full-scale RCT evaluating effects of contoured, prefabricated foot orthoses on knee pain severity and patient-perceived global change, compared to flat insoles, in adolescents with PFP. The secondary objective is to provide an estimate of treatment effects for prefabricated foot orthoses, compared to flat insoles, in adolescents with PFP.

## Methods

### Experimental design

HAPPi Kneecaps! (sHoe inserts for Adolescents with Patellofemoral PaIn) is a randomised, controlled, participant- and assessor-blind, feasibility trial, with two parallel groups. The study design was developed in consultation with the SPIRIT 2013 statement [18] and the CONSORT 2010 statement extension to randomised pilot and feasibility trials [19]. Ethics approval was obtained through The University of Queensland’s Human Research Ethics Committee (HREC No. 2018000159). The trial was prospectively registered on the Australia New Zealand Clinical Trials Registry (ACTRN12619000957190; date registered 08/07/2019). Written informed consent will be obtained from all participants prior to participation in the study.

### Participants

Adolescent volunteers with a clinical diagnosis of PFP will be recruited from the community in Brisbane, Australia. We will use an active, targeted, comprehensive recruitment strategy across multiple platforms. This strategy will integrate successful methods from our previous patellofemoral RCTs [12, 20, 21], tailored to an adolescent population. The recruitment strategy will include: (i) *social media:* we will target key social media platforms used by adolescents and their parents, using free and paid advertising (e.g. Facebook, Twitter); (ii) *secondary schools (private/public) and sports clubs (*e.g. *netball, football, athletics)* will be provided with recruitment and educational resources on PFP; (iii) *community events:* we will target key events attended by adolescents and their parents (e.g. weekend markets, community fairs) with flyers and sandwich boards. We will also recruit from our existing databases of PFP volunteers, and through contacts with health clinics (e.g. general practitioners).

Sample size has not been formally calculated for this feasibility study. Based on previous work [22, 23], we estimated that 20 participants per group (*n* = 40) would allow observation of recruitment practicalities, acceptability and common adverse effects of the interventions, dropouts, and sample variability.

Male and female adolescent volunteers will be eligible for inclusion if they meet the following criteria: (i) aged 12–18 years; (ii) anterior knee pain of non-traumatic origin that is rated at least 3 on an 11-point numerical rating scale (0 = no pain, 10 = maximal pain); (iii) knee pain aggravated by activities that load the PFJ (e.g. squatting, stair climbing, running, jumping); (iv) knee pain present at some time during most weeks; and (v) knee pain of at least 2 months duration.

Volunteers will be excluded if they meet any of the following criteria: (i) concomitant pain at sites other than the anterior knee (e.g. other knee structures, hip, lumbar spine); (ii) history of knee, hip or spine surgery, or other suspected knee joint pathology (e.g. Osgood Schlatter’s Disease); (iii) planned lower limb surgery (e.g. arthroscopy); (iv) recent treatment for PFP (e.g. knee injections or physiotherapy within the previous 3 months; foot orthoses within the previous 12 months); or (v) any foot condition precluding the use of foot orthoses.

### Study procedures

After undergoing preliminary screening for eligibility criteria via email and/or telephone, participants will be invited to undergo physical screening at The University of Queensland to confirm the presence of PFP, and absence of other anterior knee pain conditions (e.g. Osgood Schlatter’s Disease, patellar tendinopathy) (Fig. 1). Eligible volunteers (and/or their parent/guardian) will then provide written informed consent prior to collection of baseline measures. All screening procedures and baseline data collection will be performed by a registered physiotherapist ([name]), from whom group allocation will be concealed.

**Fig. 1 Fig1:**
[figure not shown]
Participant flow through the study

Participants will be randomised to one of two interventions: (i) prefabricated contoured foot orthoses, or (ii) flat shoe insoles. Randomisation procedures will be via concealed allocation, with the randomisation sequence held by an offsite investigator ([name]). Due to the nature of the two shoe insert interventions (contoured vs. flat inserts), it is not possible for study physiotherapists to be blinded to group allocation. Primary outcomes for feasibility will be collected by a blinded assessor ([name]). Secondary outcomes will be self-reported by participants, who are considered assessors. To facilitate blinding of participants (and therefore assessors of secondary outcomes) via limited disclosure, participants will be informed that they will be randomised to one of two shoe insert interventions, and will not be informed of the differences between the two inserts or the study hypotheses [12, 20].

### Interventions

The interventions will be fit by a registered physiotherapist working in a private Physiotherapy clinic in the greater Brisbane region. Study physiotherapists will be trained in fitting procedures, which will follow established algorithms [20]. Participants will receive up to four pairs of inserts fit to their daily shoes (e.g. school shoes, sports shoes, casual shoes). The inserts will be fitted to the participants’ shoes that accommodate foot orthoses and provide the best support. Fitting procedures for both the contoured and flat shoe inserts will be based on comfort, to maximise wear time and potential therapeutic effects. Participants will attend up to three appointments with the study physiotherapist to ensure adequate comfort of the inserts, and will receive written instructions for using and adapting to the inserts. Participants will be asked to wear their inserts as much as possible during their waking hours, and encouraged to transfer the inserts between different shoes as required to maximise wear time. This is consistent with current clinical practice. Participants in both groups will also receive general information and advice about PFP and activity in a participant handbook (see Additional file 1).

#### Prefabricated contoured foot orthoses

Participants randomised to the contoured foot orthoses group will receive commercially available prefabricated foot orthoses (Vasyli Medical, Labrador, Australia) (Fig. 2). These will be from the same range as the foot orthoses prescribed in our previous RCT in adults with PFP [12]. These orthoses are manufactured from ethylene-vinyl acetate (EVA) with options of a high (hard, Shore A 70°), medium (Shore A 55°) and low (soft, Shore A 45°) density, and have an inbuilt arch support and varus wedging. Modifications will be made to the foot orthoses to achieve a comfortable fit, via the addition of wedges or heat moulding as per our published algorithm [20].

**Fig. 2 Fig2:**
[figure not shown]
Prefabricated contoured foot orthoses

#### Flat shoe insoles

Participants randomised to this group will receive flat shoe inserts manufactured from high density EVA (Fig. 3). The flat insoles will be of 3 mm uniform thickness along their length, and have an identical covering fabric as the contoured foot orthoses. This is to control for any potential effects of the arch contour and wedging associated with the contoured foot orthoses. As in our previous RCT, the flat insoles will be described to participants as an intervention to enhance sensory feedback [20]. Following our fitting algorithm [20], the flat insoles will be heat moulded to enhance comfort as indicated.

**Fig. 3 Fig3:**
[figure not shown]
Flat shoe insoles (**a**), and image showing the difference in arch contouring and wedging between the flat insoles and prefabricated contoured foot orthoses (**b**)

### Adverse events

If participants experience any adverse events during the study period (e.g. excessive pressure from the shoe inserts, blistering, increase in knee pain, onset of new pain elsewhere), they will be encouraged to report these to the investigator and/or their study physiotherapist. In this event, standard clinical practice principles will be implemented. As required, participants will attend an additional appointment with their study physiotherapist. The intervention will be modified for comfort according to procedures described above. If necessary, the shoe inserts will be removed until pain settles and slowly re-introduced as the participant tolerates. Such events will be recorded as an adverse event, and participants will be followed up at regular intervals to monitor changes in symptoms and to ensure they are progressing sufficiently. If symptoms associated with the adverse event are unable to be resolved, the intervention will be ceased.

### Concomitant care

If participants are taking regular medications (e.g. anti-inflammatories), they will be permitted to continue this throughout the study duration. If at any point during the study they wish to increase or start taking pain management medication, participants will be encouraged to report this to the investigator ([name]). At the time of entry into the study, participants will be asked refrain from commencing new treatments for their knee pain for the duration of the study (e.g. therapeutic exercise), and to avoid using other assistive devices such as knee braces or other footwear interventions for the study duration. Participants will be asked to report any use of co-interventions in log books (see Additional file 2). If at any stage participants are not satisfied with their allocated intervention, they will be encouraged to report this to the investigator ([name]) for appropriate management.

### Outcome assessment

At baseline, demographic and PFP data including age, sex, weight, height, affected knee, bilaterality of PFP, symptom duration, and aggravating activities will be collected. Participants will complete patient-reported outcome measures at baseline, and at 6 weeks and 3 months post-randomisation. Data collection will largely be completed via an online platform (REDCap), but participants will have the option to complete a paper version. For the study duration, participants will be asked to keep a daily log (assisted by their parent/guardian as required) of: activities or sport completed each day, knee pain severity (rated on a 10-point numerical rating scale; 0 = no pain, 10 = worst pain imaginable), type of shoes worn that day, hours spent wearing the footwear and shoe inserts, adverse effects associated with the shoe inserts, medication use, and any other comments (see Additional file 2). Study physiotherapists will record attendance, prescription notes and adverse events during fitting and follow-up. The primary endpoint is 3 months.

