#### Primary outcomes

The primary outcome is the feasibility of conducting a full-scale RCT. Feasibility will be assessed by evaluating the following outcomes.
Willingness of participants to enroll in the study (from recruitment database).Number of eligible volunteers (from recruitment database).Recruitment rate (from recruitment database).Adherence with allocated intervention and log book completion (from Study Practitioner notes, and participant log book).Adverse events (from Study Practitioner notes, adverse events database and participant log book).Success of blinding (risk of performance and detection bias) (from *Credibility and Expectancy Questionnaire*).Drop-out rate (from trial database).

The following parameters were set to inform feasibility: (i) a recruitment rate of 1 participant per week; (ii) minimum adherence with shoe insert wear of 2 h per day, 5 days a week; and (iii) a drop-out rate of ≤20%.

Credibility and the participant’s expectations of treatment will be evaluated using the Credibility and Expectancy Questionnaire [24]. This will be completed at baseline, and at the participant’s second visit with the study physiotherapist (~ 2 weeks post-randomisation). The Credibility and Expectancy Questionnaire consists of six items organised into two sections; four items related to thoughts, and two items related to feelings. A subsequent study determined that credibility is derived from the first three thought items, and expectancy derived from the fourth thought question and the two feeling questions [25]. The Credibility and Expectancy Questionnaire has been administered in adolescent populations in previous studies [26, 27].

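### Adverse events are defined without attribution, but the daily log asks only for insert-related effects, so events not blamed on the inserts may be missed

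*Protocol article*

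**What the plan says.** Under Primary outcomes, the protocol lists adverse events among seven feasibility outcomes and names three sources: "Adverse events (from Study Practitioner notes, adverse events database and participant log book").

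The Adverse events section covers any event in the study period. Its examples are "excessive pressure from the shoe inserts, blistering, increase in knee pain, onset of new pain elsewhere", and it does not require the participant to think that the inserts were the cause. When an event occurs, "they will be encouraged to report these to the investigator and/or their study physiotherapist".

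Under Outcome assessment, the daily log collects, among other items, "knee pain severity (rated on a 10-point numerical rating scale; 0 = no pain, 10 = worst pain imaginable") and "adverse effects associated with the shoe inserts, medication use, and any other comments". The same section says: "Study physiotherapists will record attendance, prescription notes and adverse events during fitting and follow-up".

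Under Interventions, the number of contacts is variable: "Participants will attend up to three appointments with the study physiotherapist". The Adverse events section allows an additional appointment where needed.

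**The concern.** One primary outcome is collected under two scopes. The Adverse events section counts an event whatever its cause. The log, which is the only source that prompts every participant daily for harms, is described as asking only for effects of the inserts. A participant aged 12 to 18 then makes the causality judgement before anything is written down, and a symptom judged unrelated has no dedicated place in the log.

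The other routes do not clearly close the gap. One relies on the participant speaking up, and the other on the participant attending. The only physiotherapist contact with a date is the second visit, at about 2 weeks (Primary outcomes), whereas the primary endpoint is at 3 months. Log completion is itself one of the feasibility outcomes, so the plan does not take it for granted.

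At stake is the completeness of the harms description that would inform the full-scale trial. Observing common adverse effects is also part of the stated rationale for 40 participants. New pain elsewhere would be a clear signal here, because volunteers with pain at sites other than the anterior knee are excluded at entry.

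**Working it through.** The plan states no adverse-event rate, and says that its sample size was not formally calculated, so there is no figure to reproduce. The check is a comparison of the sections.

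**Step 1. Take each example in the Adverse events section and find where the plan would record it without a spontaneous report or a visit.**

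| Example | Log harm item (insert-associated) | Other routine record | Rule that makes it an adverse event |
|---|---|---|---|
| Excessive pressure | Yes | – | Recorded as such |
| Blistering | Yes | – | Recorded as such |
| Increased knee pain | Only if attributed | Daily 0 to 10 rating; pain scales at 6 weeks and 3 months; global rating of change, with three worse categories among seven | None stated |
| New pain elsewhere | Only if attributed | Open comments field | None stated |

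Two of the four are covered, one is measured but not counted by any stated rule, and one depends on free text.

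**Step 2. Check the remaining sources.**
- The adverse events database: the described inflow is reports that participants are encouraged to make, together with what physiotherapists record.
- Practitioner notes: made at fitting and follow-up, at up to three appointments plus extra ones as required, by physiotherapists who cannot be blinded (Study procedures).
- The 6-week and 3-month assessments: the outcomes listed under Secondary outcomes include no adverse-event question.
- The exit interview: by invitation, and not among the three sources named under Primary outcomes.

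**Step 3. Ask whether a size can be derived.** With true risk p and capture probability c, the expected number of participants recorded with an event in an arm of 20 is 20 × p × c. The documents give neither p nor c. The following is purely an illustration on assumed values, with c = 0.7 in both arms:
- p = 0.20: 20 × 0.20 × 0.7 = 2.8 recorded, against 4.0 with full capture.
- p = 0.30: 20 × 0.30 × 0.7 = 4.2, against 6.0.
- p = 0.40: 20 × 0.40 × 0.7 = 5.6, against 8.0.

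Equal capture lowers both counts and, because true risk is set equal in the two arms here, creates no difference between them. A spurious difference would be p × (c₁ − c₂), and nothing in the documents says that c₁ and c₂ differ, or in which direction.

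**Step 4. Put this against the precision available.** The 95% half-width for a risk difference with 20 per arm is 1.96 × √(2p(1 − p)/20). This is 0.248 at p = 0.20, 0.284 at p = 0.30 and 0.304 at p = 0.40. The trial could estimate an arm difference in adverse events only to within about 25 to 30 percentage points, even with complete capture.

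**The case against.** The strongest reply is that the log does more than its harm item suggests. Knee pain is rated every day without attribution, medication use is logged, and there is an open comments field. Knee pain is asked of everyone again at 6 weeks and 3 months, through the pain scales and the global rating of change. This stands for knee pain: the data will exist, and what is lacking is a stated rule that counts a worsening as an adverse event. It stands less well for new pain elsewhere, where free text is the only unattributed route in the log.

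A reader might go further and infer that harms will in fact be under-counted, and more so in one arm, because the contoured orthoses allow density choice, wedges and heat moulding while the flat insoles allow only heat moulding. The documents do not support that. More kinds of modification do not imply more visits, and no visit counts by arm are given. Both arms are fitted for comfort with the same ceiling of three appointments. The Credibility and Expectancy Questionnaire is due at the second visit for all participants, so a return visit is expected in both arms. The log is described identically for both arms and is kept by participants blinded through limited disclosure. Uneven capture is conceivable but cannot be shown.

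It is also fair to say that the consequence is limited. The feasibility outcomes are reported descriptively, and the three numeric criteria concern recruitment, wear time and drop-out, not adverse events.

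Finally, the log template (Additional file 2) and the online forms are not shown, and an article condenses. That limits what can be said about missing questionnaire items. It does not remove the mismatch between the two sections as written: if the template is broader, the Outcome assessment description needs correcting.

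**Conclusion.** The point holds as a mismatch of scope and a risk of incomplete capture. Adverse events are scoped without attribution in one section and, in the daily log as described in another, prompted only where associated with the inserts. The main exposure is new pain elsewhere and other events that the participant does not link to the inserts. Increased knee pain is visible in the data but has no stated route into the adverse-event count.

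No magnitude follows from the documents. The under-count could be negligible if participants use the comments field and report freely, and no arm difference can be derived. No go/no-go criterion changes. This is a cheap improvement to a primary feasibility outcome, not a threat to the trial's conclusions. It rests on the article's description of the log matching the log in use.

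**What to change.** 1. Align the log item with the scope of the Adverse events section: ask for any new or worse symptom, whether or not the participant thinks it is due to the inserts, and have study staff judge relatedness afterwards. If Additional file 2 already does this, correct the description under Outcome assessment.
2. Add the same short adverse-event checklist for all participants to the existing 6-week and 3-month questionnaires, covering the kinds of event that the protocol already names: pressure or blistering, increased knee pain, and new pain elsewhere. This also gives increased knee pain a defined route into the count.
3. Report adverse-event counts descriptively by arm and by source (log, checklist, practitioner notes, spontaneous report), so that the full-trial team can see what each source contributed.

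The cost is one reworded log field, a few tick-boxes on two existing forms, about a minute of participant time, and possibly a higher adverse-event count. No extra visits are needed.
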